### Data collection and management

#### Quantitative data collection tool

A standardised data collection template has been developed for extracting anonymised patient data from individual paper records (table 2). An online version was also made to allow for data entry on a computer or smartphone. It is estimated to take 15 min to extract data from one patient record since the records are made of blank paper with no formal structure or organisation of health data.

**Table 2 T2:** Standardised data collection form used to extract data from individual patient records

Data collection question	Answer
What is your name? (Name of person extracting data)	
Date of data extraction (MM-DD-YYYY)	
Write the clinic name	
Is this a duplicate extraction?	
If it is a duplicate extraction, enter the number you and your extraction partner have assigned to this file.	
Date of birth (MM-DD-YYYY)	
Sex (M/F)	
Smoking status (Y/M)	
Diagnosis of hypertension (Y/N)	
Date of hypertension diagnosis (MM-DD-YYYY)	
Can you find one or more blood pressure readings? (Y/N)	
Most recent systolic blood pressure	
Most recent diastolic blood pressure	
Date of the most recent blood pressure measurement (MM-DD-YYYY)	
Can you find a second most recent blood pressure reading? (Y/N)	
Second most recent systolic blood pressure	
Second most recent diastolic blood pressure	
Date of the second most recent systolic blood pressure (MM-DD-YYYY)	
Diagnosis of diabetes (type 1, type 2, no)	
Can you find one or more glycated haemoglobin (HbA1c) measurements? (Y/N)	
Most recent HbA1c reading (mmol/mol)	
Date of the most recent HbA1c measurement? (MM-DD-YYYY)	
Can you find another HbA1c measurement? (Y/N)	
Second most recent HbA1c reading (mmol/mol, otherwise specify unit)	
Date of the second most recent HbA1c reading? (MM-DD-YYYY)	
Can you find one or more total cholesterol measurements? (Y/N)	
Most recent total cholesterol reading (mmol/L)	
Date of the most recent cholesterol reading (MM-DD-YYYY)	
Can you find another cholesterol measurement? (Y/N)	
Second most recent cholesterol reading (mmol/L)	
Date of the second most recent cholesterol reading (MM-DD-YYYY)	
Was the patient prescribed a statin? (Y/N)	
What was the date of the statin prescription? (MM-DD-YYYY)	
What was the drug and dose?	
Does the patient have existing cardiovascular disease (CVD)? (Y/N)	
State the type of CVD	
Has the patient been prescribed acetylsalicylic acid (ASA or aspirin)? (Y/N)	
What was the most recent date that ASA was prescribed? (MM-DD-YYYY)	
Has the patient been prescribed antihypertensives? (Y/N)	
What was the most recent date that antihypertensives were prescribed? (MM-DD-YYYY)	
Can you find a documented ESC SCORE risk score? (Y/N)	
Enter the most recent documented ESC SCORE risk score (%)	
What was the date the risk score was documented? (MM-DD-YYYY)	
Please record any important notes about the data extraction here. Examples include an error you think may have been made, clarification of the units for measurements (eg, mmol/L vs mg/dL). Or notes that you would like for yourself.	

ESC, European Society of Cardiology.

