**Figure 1 F1:**
[figure not shown]
Illustration using the GATE frame structure^15^ of the mixed methods evaluation design. GATE, Graphic Appraisal Tool for Epidemiological studies.

A sample size of 20 primary healthcare centres was chosen because it was seen as a good balance of allowing for variation in clinic geography and demography, while still remaining feasible for the pilot implementation. Half of the centres (n=10) will be randomly allocated to the intervention arm and half (n=10) to the control arm. Baseline data will be collected from both intervention and control clinics, ensuring that baseline data are collected before implementation occurs.

Within clinic comparisons will be used to compare the 12 months before randomisation with the 12 months of implementation. Between clinics comparison will be used to compare the intervention clinics with control clinics during the same time period.

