Are statins prescribed correctly based on documented risk score?	Proportion of patients eligible based on documented risk score prescribed a statin.	Patients with a documented risk score as very high risk SCORE≥15% prescribed a statin.	Patients with a documented risk score as very high risk SCORE≥15%.
Are patients with existing disease, who do not require the calculation of a risk score to prescribe satins, prescribed statins?	Proportion of patients with existing CVD prescribed a statin.	Patients with existing CVD prescribed a statin.	Patients with existing CVD.
Is the blood pressure of high-risk patients controlled?	Proportion of high-risk patients (SCORE≥15% or DM and age over 40 years) whose last two recorded blood pressure measurements were <130/80 mm Hg.	Patients with a true risk score indicating a very high risk (SCORE≥15%) or DM and age over 40 years whose last two documented blood pressure readings were <130/80 mm Hg.	Patients with a true risk score indicating a very high risk (SCORE≥15%) or DM and age over 40 years.
Is the blood pressure of low-risk patients controlled?	Proportion of low-risk patients (SCORE<15%) whose last two recorded blood pressure measurements were <140/90 mm Hg.	Patients with a true risk score indicating <15% whose last two documented blood pressure readings were <140/90 mm Hg.	Patients with a true risk score indicating <15%.
Are patients with existing CVD prescribed basic medications to reduce risk?	Proportion of patients with existing CVD prescribed a statin and aspirin and blood pressure-lowering treatment.	Patients with existing CVD prescribed a statin and aspirin and blood pressure-lowering treatment.	Patients with existing CVD.
Is the blood glucose of patients with diabetes controlled?	Proportion of patients with diabetes with glycaemic control as defined by last two HbA1c measurements.	Patients with type 2 diabetes whose last two HbA1c measurements were below personal target as defined by MDA-adapted WHO PEN protocol 1.	Patients with type 2 diabetes.
Is the blood pressure of patients with hypertension controlled?	Proportion of patients with confirmed hypertension whose systolic blood pressure is <140/90 mm Hg at last two visits.	Patients with confirmed hypertension whose last two blood pressure readings were <140/90 mm Hg.	Patients with confirmed hypertension.

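### The statin date item is not tied to the most recent prescription, no item asks about a documented stop, and Table 1 sets no time window, so statin prescribing cannot be reliably placed in the baseline or implementation year.

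*Protocol article*

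**What the plan says.** All references are to the protocol article.

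**Table 2 (Quantitative data collection tool).** Each drug gets a yes/no item and one date.
- Statin: "Was the patient prescribed a statin? (Y/N", then "What was the date of the statin prescription? (MM-DD-YYYY", then "What was the drug and dose".
- Aspirin: "Has the patient been prescribed acetylsalicylic acid (ASA or aspirin)? (Y/N", then "What was the most recent date that ASA was prescribed? (MM-DD-YYYY".
- Antihypertensives: a yes/no item, then "What was the most recent date that antihypertensives were prescribed? (MM-DD-YYYY".

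No structured item asks whether a drug was stopped. A free-text notes field closes the form.

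**Table 1 (Quantitative indicators).** Four of the 14 indicators use statin prescription: all eligible patients, patients with a documented SCORE of at least 15%, patients with existing CVD, and the composite of "patients with existing CVD prescribed a statin and aspirin and blood pressure-lowering treatment". None of these numerators says when the prescription must have been written. The risk-factor indicator, by contrast, carries a 12-month limit.

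**Methodological design.** "Within clinic comparisons will be used to compare the 12 months before randomisation with the 12 months of implementation". Intervention and control clinics are also compared over the same period.

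**The concern.** To compare one 12-month period with another, each prescription has to be placed in a period. The form does not secure this for statins. The yes/no item has no time limit, and the date item does not say which prescription it means. A patient prescribed a statin years ago and since taken off it meets the numerator as written. A patient treated for years may be dated by the start or by the latest prescription, depending on the extractor. The drug-and-dose item has the same gap.

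At stake are the secondary objective of estimating change against control clinics and, in part, the primary objective of learning whether these records can supply data for later effectiveness studies. An analysis plan can define a window afterwards. It cannot recover which prescription an extractor dated, or a stop that nobody was asked to look for.

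**Working it through.** The plan states no figure on this point, so there is none to reproduce. The check sets the form against the indicators, followed by two illustrations on assumed inputs.

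**1. Form against indicators**

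| Drug | Yes/no item limited in time? | Date asked for | Stop prompted? | Table 1 window? |
|---|---|---|---|---|
| Statin | No | Unspecified | No | None |
| Aspirin | No | Most recent | No | None |
| Antihypertensive | No | Most recent | No | None |

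Blood pressure, HbA1c, cholesterol and the risk score are also tied to the most recent value. Among the dated measurements and prescriptions, only the statin entry lacks that anchor.

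For aspirin and antihypertensives, the date together with the extraction date allows a 12-month restriction. It captures a re-prescription but cannot separate a restart from a refill. For statins the restriction works only if the latest date happened to be entered. The composite therefore joins one ambiguous date to two most-recent dates.

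**2. Effect on the level, no window applied.** Let *s* be the share of patients recorded as prescribed whose drug has since been stopped. The documents give no value, so *s* is assumed. Recorded ÷ current = 1/(1 − s).
- s = 10%: 1/0.90 = 1.11; a recorded 50% means 45% current.
- s = 20%: 1/0.80 = 1.25; 50% means 40%.
- s = 30%: 1/0.70 = 1.43; 50% means 35%.

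**3. Effect on the contrast.** Assume 100 CVD patients per arm, 50 ever prescribed a statin and 15 of them stopped, so 50 − 15 = 35 currently prescribed in the control arm. Suppose the intervention raises this by 10, to 45. The true odds ratio is (45/55)/(35/65) = 1.52 and the true difference is 10 points.

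- *No window; the extra 10 are restarts.* Both arms record 50%, so the odds ratio is 1.0 and the difference is 0.
- *12-month window, latest date entered; the extra 10 are restarts; earlier stops predate the period; continuing users have a prescription in the year.* 45% against 35%: the contrast is recovered.
- *12-month window, start date outside the period entered for half of the continuing users; the extra 10 are new starts.* Control 0.5 × 35 = 17.5%; intervention 17.5 + 10 = 27.5%. Odds ratio (27.5/72.5)/(17.5/82.5) = 1.79; the difference stays at 10 points.
- *As the previous case, but the extra 10 are restarts and half of them also carry the old start date.* Intervention 17.5 + 5 = 22.5%. Odds ratio (22.5/77.5)/(17.5/82.5) = 1.37; difference 5 points.

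The same true effect can thus be erased, recovered, inflated or diluted, according to a reading that the form leaves open. Every input in steps 2 and 3 is an assumption. The scenarios show that the direction is undetermined; they do not estimate what happened.

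**The case against.** The strongest case against is that this is a one-phrase wording mismatch in a pilot. Its parts deserve separate answers.

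- **The indicators measure prescribing.** The article classes prescribing as an output indicator and does not claim to measure drugs taken. This stands: a reader might infer that stopped patients are counted as treated, but the documents support only that they are counted as prescribed. It does not answer the missing period, because prescribing within a given year still has to be dated to that year.
- **Stops and restarts are not wholly hidden.** A reader might infer that the form can never show a stop and that restarts are invisible. That goes too far. The notes field can hold a stop, though nothing prompts it, and the most-recent dates for aspirin and antihypertensives pick up a re-prescription. Even the statin item would, if the latest date were entered.
- **The zero effect needs a missing window.** This stands. A real gain is recorded as no change only when no window is applied and the gain consists of restarts. With a window and the latest date, what remains of the stop problem is patients prescribed and then stopped within the same 12 months.
- **Both arms use the same form.** Baseline extraction precedes randomisation, and follow-up uses the same instrument in all 20 centres. No bias towards one arm is shown. A common instrument does not make the error cancel, however, since its effect depends on the mix of new, continuing and restarted users.
- **Trained extractors and duplicate extraction may help.** Duplicates can reveal inconsistent statin dates, and fuller instructions may exist outside the article. But Table 2 is presented as the form itself, and the records are unstructured paper, so the wording of the item matters.

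**Conclusion.** The point holds in a limited form. The statin date is inconsistent with the other two drugs and ambiguous, no item prompts for a stop, and four of 14 numerators have no window although two 12-month periods are compared. As written, old or discontinued statin prescriptions count, and a statin prescription cannot be reliably assigned to a period. Levels are inflated and the change can be blurred.

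The size is unknown. The factor of 1.11 to 1.43 rests on an assumed 10% to 30% of recorded users having stopped and on no window being applied. The direction of any error in the between-arm contrast is also unknown. A reader should not infer that the comparison favours one arm or that a true effect would necessarily be recorded as nil; the documents support neither. This should be corrected because it is cheap and cannot be repaired after extraction. It does not invalidate the pilot.

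**What to change.** 1. **Table 2, statin items:** ask for the most recent statin prescription and for the drug and dose of that prescription, matching the other two drugs.
2. **Table 2, all three drugs:** add one item on whether the record documents that the drug was stopped after that date (yes/no, date).
3. **Table 1:** state that a prescription counts if it was issued, or is documented as continuing, within the 12-month comparison period with no later recorded stop. Apply this to each of the three drugs in the composite. The continuing clause matters: without it, long-standing users with no new prescription written that year would be dropped. The extractor instructions should say how to enter a documented continuation.
4. **Comparability:** use the same items in both arms and both rounds. If baseline data were already collected on the current form, keep the original items beside the new ones and report the original definition as well.

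The cost is a somewhat longer extraction than the estimated 15 minutes per record. The added time is not known, since searching unstructured charts for stops may be slow. Stated prescribing rates will be lower, and stops never written in the chart will still be missed.

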#### Method of randomly sampling patient records

A random sample of the records of patients aged over 18 years, who have visited the medical facility within the past 12 months, will be taken. Since medical records in MDA are organised alphabetically on shelves, we created a randomly generated list of alphanumeric combinations that allowed for the selection of patient charts at random. For example, an alphanumeric code of ‘C24’ would correspond to the 24th patient chart in the section of last names starting with the letter C.

The list will be followed in the order that it was generated so as to prevent selection bias. The randomly selected chart will then be checked to see if it meets two inclusion criteria^1^: the patient is aged 18 years or older and^2^ the patient visited the health centre within the last 12 months. If the record meets these criteria, data will then be extracted. If it does not, it will be returned to the shelf and the next alphanumeric code on the randomly generated list will be used. This process will be repeated in each clinic until a sample size of 1.2% of the patient population in each clinic is sampled. This proportion was chosen pragmatically such that the average sample per primary healthcare centre would equal 100 unique patients.

#### Data analysis

The change in indicators from baseline to follow-up will be calculated for intervention clinics and compared with control clinics (table 1). Subgroup analysis by age, gender and other demographic features may be done as deemed appropriate by the national steering committee. All analyses will account for stratified sampling. Since the health centre is the unit of inference for the outcomes (eg, health centre proportion of eligible patients with a documented CVD risk score), use of an intracluster correlation coefficient is not required for analyses of these outcomes. Age-adjusted and gender-adjusted logistic regression models will be used to analyse the differences in predefined indicators between intervention and control clinics and between baseline and follow-up. The differences in means of continuous variables between the intervention and control clinics and baseline and follow-up will be analysed using age-adjusted and gender-adjusted analysis of variance.

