### Objectives

#### Primary objectives

Assess the ability to implement MDA-adapted WHO PEN protocols 1 and 2 in pilot primary healthcare centres.Determine the feasibility of collecting quantitative data required for future studies of effectiveness from the existing informal paper clinical record system.

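### The Data analysis section waives the intracluster correlation because the clinic is the unit of inference, then names models naturally read as running on individual records with no clinic term; the intervals would be too narrow by an amount that depends on the ICC, the denominator and the contrast

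*Protocol article*

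**What the plan says.** Clinics are the randomised units. The text under Figure 1 states: "Half of the centres (n=10) will be randomly allocated to the intervention arm and half (n=10) to the control arm". The Randomisation section stratifies them by the ratio of patients to family doctors.

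Records are sampled within each clinic "until a sample size of 1.2% of the patient population in each clinic is sampled", a fraction chosen so that "the average sample per primary healthcare centre would equal 100 unique patients" (Method of randomly sampling patient records). The same is done at baseline and at 12 months.

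The Data analysis section then makes three statements:

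- "Since the health centre is the unit of inference for the outcomes", with a clinic-level proportion given as the example, "use of an intracluster correlation coefficient is not required for analyses of these outcomes".
- For the indicators, the text goes on to name the method: "Age-adjusted and gender-adjusted logistic regression models will be used to analyse the differences in predefined indicators between intervention and control clinics". The same models serve to compare the two rounds.
- Differences in means of continuous variables are "analysed using age-adjusted and gender-adjusted analysis of variance".

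The only design feature that the section promises to allow for is stratification of the sample. It names no random effect for clinic, no GEE, no cluster-robust variance, and no step that reduces the records to clinic summaries.

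**The concern.** The waiver is sound for one kind of analysis: each clinic contributes a single summary per round and 10 values are compared with 10. Between-clinic variation then sits in the error term, and no separate ICC is needed. The models named next are of another kind. Age and gender belong to patients, and the extraction form (Table 2) takes date of birth and sex from each record, so adjusting for them points to a regression on individual records. A regression without a clinic term treats records from the same clinic as independent. Chance differences between clinics, which randomising 10 per arm cannot average out, would then be counted as evidence about the intervention.

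At stake is the precision reported for the second of the secondary objectives, the change in pilot clinics compared with control clinics. That result feeds the assessment of whether national scale-up is feasible.

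**Working it through.** **Inputs from the protocol article.** Ten clinics per arm; on average 100 records per clinic per round, so 10 × 100 = 1,000 per arm and 2,000 per round. The article gives no alpha, ICC or power figure, so there is no stated figure to reproduce.

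**Assumptions.** Two-sided 5% level; ICC 0.02, 0.05 and 0.10, with 0.001 as a low bound; for the change contrast, a correlation r = 0.8 between a clinic's true level at baseline and at follow-up. The number m of records per clinic in an indicator's denominator is 100 only where all sampled adults count. In Table 1 that is 1 of the 14 indicators, the prevalence of high blood pressure. The other 13 are restricted (age 40 or older, complete measurements, documented score, existing CVD, type 2 diabetes, hypertension, SCORE bands), so m = 50 and m = 20 are shown as assumed values.

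**Formulas.**

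- Follow-up comparison between arms: DE = 1 + (m − 1) × ICC.
- Change from baseline, with separate record samples in each round: DE = 1 + (m − 1) × ICC − m × ICC × r.
- Actual type I error of the unclustered test: 2 × [1 − Φ(1.96/√DE)].
- Width of the unclustered interval relative to the correct one, before any small-sample correction: 1/√DE.

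**Worked example.** With m = 100 and ICC 0.05, DE = 1 + 99 × 0.05 = 5.95. Then 1.96/√5.95 = 0.80, the type I error is 42%, and the width is 1/√5.95 = 41% of the correct one.

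| Contrast | m | DE at ICC 0.02 / 0.05 / 0.10 | Type I error |
|---|---|---|---|
| Follow-up, between arms | 100 | 2.98 / 5.95 / 10.9 | 26% / 42% / 55% |
| Follow-up, between arms | 50 | 1.98 / 3.45 / 5.9 | 16% / 29% / 42% |
| Follow-up, between arms | 20 | 1.38 / 1.95 / 2.9 | 10% / 16% / 25% |
| Change, r = 0.8 | 100 | 1.38 / 1.95 / 2.9 | 10% / 16% / 25% |
| Change, r = 0.8 | 50 | 1.18 / 1.45 / 1.9 | 7% / 10% / 16% |
| Change, r = 0.8 | 20 | 1.06 / 1.15 / 1.30 | 6% / 7% / 9% |

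**Sensitivity.** At ICC 0.001 and m = 100, DE = 1.10 and the follow-up type I error is 6.2%, which is negligible inflation. For the change contrast at m = 100 and ICC 0.05, the error is 29% at r = 0.5, 10% at r = 0.9 and about 4% at r = 1.

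**In percentage points**, for the follow-up comparison at m = 100 and 50% prevalence. The unclustered half-width is 1.96 × √(2 × 0.25/1000) = 4.4 points. The clinic-level half-width, with t on 18 degrees of freedom (2.10), is 2.10 × √(2 × 0.25 × DE/1000) = 8.1 / 11.5 / 15.5 points for ICC 0.02 / 0.05 / 0.10.

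**Check by simulation**, 10 v 10 clinics of 100 records, no true effect. Unclustered logistic tests (2,000 runs per setting, prevalence 10% to 50%) rejected in 41–43% at ICC 0.05 and 53–57% at 0.10. Age- and sex-adjusted logistic regression on records (500 runs, ICC on the latent scale) rejected in 35% and 50%. A t-test on the clinic proportions rejected in 4.4–5.6% over ICC 0.01 to 0.10.

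**The case against.** The text never says that the models run on individual records. Its example outcome is a clinic proportion, and an adjusted model followed by clinic summaries would be compatible with the wording. This stands as a caution: the patient-level reading is the natural one, not a certain one. It does not remove the problem. Logistic regression on clinic counts, with binomial variance and no clinic term, has the same fault. Analysis of variance on 20 clinic means would be valid, but it is not specified. Nor does the promise to allow for stratification help. Strata of patients per doctor are not clinics, and treating the clinics as fixed strata would take the between-clinic variance out of the error term.

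A reader might infer that all the intervals are far too narrow and the false-positive rates several times nominal. The documents do not support that without conditions. The largest figures need 100 records per clinic, which fits one indicator, and the follow-up comparison. The Data analysis section opens with change from baseline, where the inflation is much smaller. The follow-up figures still matter, because the text under Figure 1 also plans a comparison of the arms over the same period.

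A reader might also infer that the pilot was set up to supply an ICC, or that scale-up turns on a p-value. Neither is stated. The primary objectives are the ability to implement the protocols and to "Determine the feasibility of collecting quantitative data required for future studies of effectiveness" from the paper records. The waiver concerns the analysis of the outcomes and does not rule out estimating an ICC. No significance criterion is given, the sample size is openly pragmatic, and the qualitative strand has equal weight.

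**Conclusion.** The concern holds as an internal contradiction that must be resolved. The justification fits a clinic-level analysis; the methods named after it do not, on their natural reading. Applied to records without a clinic term, they give intervals that are too narrow whenever the ICC is appreciable and clinic effects are not fully stable between rounds. Over ICC 0.02 to 0.10, the type I error ranges from about 6% (change from baseline, 20 records per clinic, r = 0.8) to about 55% (follow-up comparison, 100 records per clinic). The 5% level, ICC, autocorrelation and restricted denominators are all assumptions. That the comparison is a secondary objective of a feasibility pilot limits the consequence; it does not make the intervals valid.

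**What to change.** Make the analysis match the randomised unit, for binary and continuous outcomes alike, by one of two routes:

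- **(a) Two-stage, clinic-level.** Form age- and sex-adjusted clinic summaries, then compare 10 v 10 with a t-based method, on follow-up values or on change, adjusting for the patients-per-doctor stratifier. The waiver may stay, but must be tied expressly to this analysis.
- **(b) Model-based.** Use mixed logistic and linear models with clinic and clinic-by-period effects, or GEE, with a small-sample correction and the stratifier included. The waiver must then be deleted.

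Reporting each indicator's ICC with a confidence interval would be a useful extra output for planning later effectiveness studies. It is a suggestion and does not correct a stated objective.

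The cost is a change of analysis wording and wider intervals. No new data are needed.
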